**Figure 3 F3:**
[figure not shown]
**Schematic illustration of the four training groups**. Using this design we can compare the effectiveness of both time-wise combinations of training and the influence of training supervision.

1) There is no difference between the groups 1WS, 3WS, 9WS and reference for the change in neck/shoulder pain from baseline to week 20.

2) There is no difference between the groups 3WS, 3MS and reference for the change in neck/shoulder pain from baseline to week 20.

Power analyses performed prior to the study showed that - to reject the null-hypothesis of equality - we should include 150 participants per group (allowing for a 20% loss to follow-up) for 80% power to detect a 10% change in pain between groups.

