1) the effect of different time wise combinations of training with identical accumulated duration, in order to elucidate possible ranges of training effectiveness and flexibility

2) the relevance of training supervision for safe and effective training, in order to minimize expenses for workplace physical exercise training.

The concept of 'intelligent physical exercise' is to balance the physiological capacity relatively to occupational exposure, tailor the exercise to individual capacities and disorders, allow for flexibility and interest for the participant, and to be as cost-effective for the company as possible.

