### Statistics

The primary outcome is change in pain of the neck and shoulders at 20 weeks. Secondary outcomes include the other measures mentioned above. We plan to analyze the main data according to the intention-to-treat principle. Secondly, we will also analyze data per protocol. We will use repeated measures analysis of variance. Our design allows us to compare both the effect of different combination of duration and frequency and the effect of training supervision (figure 3). The following null-hypotheses will be tested;

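### Both stated null hypotheses are joint equalities that include the no-training reference, and no hypothesis between training groups is stated, so rejecting either one does not isolate a schedule or a supervision effect

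*Protocol article*

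**What the plan says.** The Background section of the protocol article gives two aims. The first is "the effect of different time wise combinations of training with identical accumulated duration". The second is "the relevance of training supervision for safe and effective training", with lower cost to the workplace as the stated purpose.

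The Statistics section makes change in neck and shoulder pain at 20 weeks the primary outcome and claims: "Our design allows us to compare both the effect of different combination of duration and frequency and the effect of training supervision". The method is given in one sentence: "We will use repeated measures analysis of variance". Two null hypotheses are then listed as those that will be tested:

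- H1: "There is no difference between the groups 1WS, 3WS, 9WS and reference for the change in neck/shoulder pain from baseline to week 20".
- H2: "There is no difference between the groups 3WS, 3MS and reference for the change in neck/shoulder pain from baseline to week 20".

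The power statement that follows asks for 150 participants per group, allowing for 20% loss, to give 80% power for a 10% change in pain between groups. It does not say which groups, or 10% of what. The article does not call H1 and H2 primary; they are the hypotheses stated for the primary outcome.

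**The concern.** Aim 1 is a question among three training groups. Aim 2 is a question between two. Each hypothesis adds the untrained group and tests all members jointly. The article's Background describes specific strength training as the most promising exercise type for neck pain, so a general benefit over no training is a likely state of affairs. In that state both H1 and H2 are false even if schedule and supervision are irrelevant, and both will tend to be rejected.

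A reader who sees H1 rejected under the aim about schedules could take it as evidence that schedule matters, and likewise H2 for supervision. Non-rejection does not help either, because it does not show that the groups are similar. A workplace choosing a convenient schedule or less supervision needs the size of the difference between training groups, with its uncertainty.

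**Working it through.** **Inputs**

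- Group sizes (Table 2): 1WS 115, 3WS 122, 9WS 113, 3MS 126, reference 97; total 573.
- Loss of 20% (power statement): multiplying by 0.8 gives 92, 97.6, 90.4, 100.8 and 77.6.
- Assumed, not in the article: two-sided alpha 0.05, equal SDs, a one-way comparison of change scores, no clustering (no intracluster correlation is given).
- Assumed benefit: the standardised difference that 150 × 0.8 = 120 evaluable per group detects pairwise with 80% power. The normal approximation is (1.960 + 0.842) × √(2/120) = 0.362; the t-based value is 0.363. This is derived, not a plan figure.

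**The plan's own figure.** The 150 per group cannot be reproduced, because the SD, alpha and meaning of 10% are not given. If 10% means 0.9 points of the 0–9 scale, two-sided 0.05 and 20% loss give 118, 129 or 140 per group for SD 2.2, 2.3 or 2.4 (the range of the neck-pain SDs in Table 2), and 153 for SD 2.5. If it means 10% of a baseline of 3.2 (0.32 points), SD 2.3 gives 1014. The 150 fits a pairwise comparison on the first reading with an SD near 2.5, but the article does not say so.

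**Formula.** With means μᵢ in SD units and weighted mean μ̄, λ = Σ nᵢ(μᵢ − μ̄)². The rejection probability is P[F(k−1, N−k; λ) > F₀.₉₅]. Where one set of groups (total n_A) is shifted by d from the rest (total n_B), λ = d² × n_A × n_B / N. Here d² = 0.363² = 0.1318.

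**All training groups equally effective (no schedule or supervision effect)**

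- H1: n_A = 92 + 97.6 + 90.4 = 280, n_B = 77.6, N = 357.6. λ = 0.1318 × 280 × 77.6 / 357.6 = 8.01; critical F 2.63; rejection 0.649.
- H2: n_A = 97.6 + 100.8 = 198.4, n_B = 77.6, N = 276. λ = 0.1318 × 198.4 × 77.6 / 276 = 7.35; critical F 3.03; rejection 0.673.
- A test of 1WS = 3WS = 9WS alone has λ = 0 here and rejects at 0.05.

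**A real supervision or schedule difference**

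- Only 3WS works and 3MS equals reference: H2 has λ = 0.1318 × 97.6 × 178.4 / 276 = 8.31; rejection 0.730.
- One schedule works and the other two equal reference: H1 has λ from 8.90 to 9.35 depending on the schedule; rejection 0.70 to 0.72.

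**Sensitivity**

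- At 0.5 SD with the same sizes, a uniform benefit rejects H1 with probability 0.917 and H2 with 0.924.
- At the planned 120 evaluable per group, with 0.9 points and SD 2.3 (d = 0.391), a uniform benefit rejects H1 with probability 0.888 and H2 with 0.887. If only 3WS works, H2 is again rejected with probability 0.887: both cases have λ = d² × 120 × 240 / 360 = 12.25.
- On the same assumptions, schedule benefits of 0.9, 0.45 and 0 around a reference at 0.45 (training on average no better than no training) still reject H1 with probability 0.717.

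Clustering would divide every λ by a design effect. That lowers all these probabilities but does not make the tests distinguish the cases.

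**The case against.** Four points can be made for the plan.

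- **An omnibus test followed by contrasts is conventional.** The article says it means to compare schedules and supervision, and the contrasts may be listed in a full protocol or analysis plan that is not shown. This stands in part: it cannot be inferred that the trial has no such contrasts. But the article states which hypotheses will be tested, and neither matches an aim. That is a stated rule, not a missing detail.

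- **The reference group belongs in the aims.** Aim 1 also speaks of the range of effectiveness, aim 2 of training that is effective, and the Background asks for the least supervision that still works. Whether 3MS works at all needs the reference group. This stands, and is why comparisons with reference should be kept, but as separate tests.

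- **Rejection does carry information on schedule and supervision.** This is correct. A reader might infer that rejecting H1 or H2 only shows that training beats no training. The documents do not support that: equality of schedules and equality of supervision levels are components of the joint nulls, and a difference in either can cause rejection, as the 0.72 example shows. Rejection establishes neither a general training effect nor a schedule or supervision effect.

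- **No claim of similarity is planned.** The article states no equivalence hypothesis and no margin. A reader might want to use the 10% as a margin, but it is undefined. Taken as 0.9 points, with an assumed design effect of 1.12, the 3WS minus 3MS interval would have a half-width of 1.96 × SD × √(1.12 × (1/97.6 + 1/100.8)), which is 0.59 at SD 2.0 and 0.68 at SD 2.3. It would lie within ±0.9 only about 70% (SD 2.0) or 48% (SD 2.3) of the time under exact equality. The interval is worth reporting, but the 10% should not be turned into an equivalence criterion.

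**Conclusion.** The point holds in this form: H1 and H2, as written, do not isolate the schedule effect or the supervision effect, and no hypothesis between training groups is stated. Under the assumptions shown, a uniform 0.363 SD benefit of training rejects H1 and H2 about 65% and 67% of the time with no schedule or supervision difference. H2 is rejected about 73% of the time if only supervised training works. Rejection of H2 is therefore nearly as likely under either answer to aim 2, and equally likely (0.89) at the planned group sizes with 0.9 points and SD 2.3.

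That the hypotheses do not match the aims follows from the text and needs no assumption. The percentages depend on alpha, effect size, SD and loss, which the article leaves partly or wholly undefined, and they ignore clustering; they are illustrations. It would go too far to say that the trial cannot answer its questions. The design supports the right contrasts, and only the stated hypotheses fail to name them.

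**What to change.** Restate the hypotheses for the change in pain from baseline to week 20 as follows.

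1. Schedule: 1WS = 3WS = 9WS among the supervised training groups (2-df test), with pairwise differences.
2. Supervision: the contrast 3WS minus 3MS.
3. Effectiveness: each training group against reference, tested separately from 1 and 2.

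Estimate all of these from one model that accounts for the cluster randomization, and report each with a 95% confidence interval. State before analysis a testing order or a multiplicity rule, since two joint tests become several contrasts. State also that similarity of schedules or supervision levels will not be concluded from a non-significant test, and that the interval will be reported instead.

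The cost is rewording, a few contrast statements in the same model and the multiplicity rule, which may take some power from individual contrasts. No extra data are needed.
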